# A combination of ascorbic acid and α-tocopherol to test the effectiveness and safety in the fragile X syndrome: study protocol for a phase II, randomized, placebo-controlled trial

**DOI:** 10.1186/1745-6215-15-345

**Published:** 2014-09-03

**Keywords:** Antioxidants, Experimental treatment, Fragile X syndrome, Oxidative stress, Trial

## Abstract

**Background:**

Fragile X syndrome (FXS) is an inherited neurodevelopmental condition characterised by behavioural, learning disabilities, phisical and neurological symptoms. In addition, an important degree of comorbidity with autism is also present. Considered a rare disorder affecting both genders, it first becomes apparent during childhood with displays of language delay and behavioural symptoms.

Main aim: To show whether the combination of 10 mg/kg/day of ascorbic acid (vitamin C) and 10 mg/kg/day of α-tocopherol (vitamin E) reduces FXS symptoms among male patients ages 6 to 18 years compared to placebo treatment, as measured on the standardized rating scales at baseline, and after 12 and 24 weeks of treatment.

Secondary aims: To assess the safety of the treatment. To describe behavioural and cognitive changes revealed by the Developmental Behaviour Checklist Short Form (DBC-P24) and the Wechsler Intelligence Scale for Children–Revised. To describe metabolic changes revealed by blood analysis. To measure treatment impact at home and in an academic environment.

**Methods/Design:**

A phase II randomized, double-blind pilot clinical trial. Scope: male children and adolescents diagnosed with FXS, in accordance with a standardized molecular biology test, who met all the inclusion criteria and none of the exclusion criteria. Instrumentation: clinical data, blood analysis, Wechsler Intelligence Scale for Children–Revised, Conners parent and teacher rating scale scores and the DBC-P24 results will be obtained at the baseline (t0). Follow up examinations will take place at 12 weeks (t1) and 24 weeks (t2) of treatment.

**Discussion:**

A limited number of clinical trials have been carried out on children with FXS, but more are necessary as current treatment possibilities are insufficient and often provoke side effects. In the present study, we sought to overcome possible methodological problems by conducting a phase II pilot study in order to calculate the relevant statistical parameters and determine the safety of the proposed treatment. The results will provide evidence to improve hyperactivity control and reduce behavioural and learning problems using ascorbic acid (vitamin C) and α-tocopherol (vitamin E). The study protocol was approved by the Regional Government Committee for Clinical Trials in Andalusia and the Spanish agency for drugs and health products.

**Trial registration:**

ClinicalTrials.gov Identifier: NCT01329770 (29 March 2011)

## Background

Fragile X syndrome (FXS) was first described by Martin and Bell in 1943 in families with several males affected by sex-linked mental retardation [1]. It later was identified as the most common cause of inherited mental retardation [2–4]. The prevalence of FXS has been estimated at 1 in 2,500 males and 1 in 4,000 females [5, 6].

In addition to moderate to severe mental retardation, individuals with FXS exhibit macroorchidism—an elongated face, long ears, connective tissue dysplasia, hyperactivity, autistic-like and stereotypical behaviours, speech delay and increased sensory sensitivity [7, 8]. Neuropathological features of FXS are a long, thin, tortuous appearance of cortical dendritic spines, increased intracranial volume, enlarged ventricles, increased volume of selective subcortical grey-matter regions and decreased size of the posterior cerebellar vermis [9], and, in a mouse model, altered glucose metabolism [10].

The name *fragile X syndrome* came into existence upon the discovery of a fragile site in the long arm of the X chromosome detected by cytogenetic testing in a cell culture medium deprived of folic acid [11]. The fragile X mental retardation 1 (*FMR1*) gene was linked to the region (Xq27.3), and a dynamic CGG repeat expansion mutation was identified as the cause of the syndrome [12]. A full mutation with more than 200 CGG repeats causes methylation of *FMR1* and leads to transcriptional silencing of the gene [13]. It has been established that a normal range of CGG repeats varies between 6 and 55, and a CGG expansion over this range is considered abnormal. An unstable premutation allele consists of more than 55 CGG repeats, resulting in reduced levels of the fragile X mental retardation 1 protein (FMRP) encoded by *FMR1*, despite a larger quantity of its mRNA. This may be due to a compensatory mechanism derived from a translation problem in the premutated mRNA [14]. A late-onset neurodegenerative disorder that causes intention tremor, problems with coordination and balance (cerebellar ataxia) and cognitive disability has been described in males and females older than 50 to 55 years of age who are carriers of a premutation allele. This disorder is known as fragile X premutation tremor/ataxia syndrome, which is caused by an increased level of mRNA that leads to neurotoxicity in the brain [15].

The physiological effects of FMRP are not well understood, and the mechanisms that explain the pathogenesis of this syndrome remain unclear. FMRP is an mRNA binding protein and it forms complexes with additional proteins to transport target mRNA from the nucleus to the cytoplasm in microtubule-dependent movements that drive the complexes to the neurites in PC12 cells stimulated by nerve growth factor [16].

There is evidence that FXS is associated with alterations in the action of the hypothalamic-pituitary-adrenal axis [17, 18]. Recently, abnormalities in glucocorticoid secretion were shown in people with FXS and the FXS *Fmr1*-knockout mouse model [19, 20]. Also, an abnormal catecholamine content was demonstrated in this mouse model [21].

Our previous results indicate that an excess of Rac1-GTPase activation leads to nicotinamide adenine dinucleotide phosphate (NADPH) oxidase–dependent activation and high levels of free radical production in the *Fmr1-*knockout mouse brain. Elevated oxidative stress and alterations in the antioxidant system, including glutathione (GSH) decrease, are observed in the *Fmr1-*knockout brain [22]. Brain redox dysregulation alters emotion-related behaviours but leaves spatial abilities intact. Thus, a GSH deficit affects parvalbumin immunoreactive interneuron integrity and neuronal synchrony in a region- and time-specific manner, leading to behavioural phenotypes related to psychiatric disorders [23].

The central nervous system is highly sensitive to oxidative stress due to its specific anatomical and physiological characteristics. Neurons consume oxygen to produce ATP to maintain intracellular gradients of different ions (K^+^, Na^+^, Ca^2+^). Neurons are postmitotic cells that are very sensitive to oxidation. Free radicals from oxygen and nitrogen (reactive oxygen species (ROS) and reactive nitrogen species) are involved in redox regulation of several protein functions, such as glutamate transporters and neurotransmitter receptors, leading to excitotoxicity processes in the long term. This can change cellular functions and lead to long-term cell death [24].

It is well known that redox regulation is involved in many important cellular mechanisms in neurons, astrocytes and microglia, such as the activation of the mitogen-activated protein kinase (MAPK) cascade (extracellular signal-related kinase 1/2 (ERK1/2), c-Jun N-terminal kinase 1/2, p38MAPK), Ca^2+^ release and the activation of apoptotic processes [25, 26]. ROS produced by mitochondrial proteins or membrane proteins (such as NADPH oxidase activated by Rac1) have a role in physiological plasticity and may be required for normal cognitive functions [27]. An excess of ROS, however, may induce harmful changes in cellular physiology, and cells can be protected from oxidation with antioxidant processes and detoxification, such as the activation of the glutathione system. GSH plays a critical role as an antioxidant, enzyme cofactor, cysteine storage form and the major redox buffer, and it is a neuromodulator in the central nervous system. One of its most important roles is serving as a carrier/storage form for cysteine. Cysteine itself has neurotoxic effects mediated by free radical generation, which increases extracellular glutamate and triggers the overactivation of *N*-methyl-D-aspartate (NMDA) receptors. It can also serve as a neuromodulator/neurotransmitter and binds via its γ-glutamyl moiety to NMDA receptors [28]. In addition, it is thought to exert dual (agonistic and antagonistic) actions on neuronal responses mediated by NMDA receptors in the brain. GSH also serves as an endogenous nitric oxide (NO) reservoir to form *S*-nitrosoglutathione (GSNO). GSNO can release NO under certain conditions with biological effects, whereas it has a protective effect in the brain under oxidative stress conditions [29]. In addition, it is required for cell proliferation and neuronal differentiation [30].

GSH deficiency has been implicated in neurodegenerative diseases. It is a tripeptide composed of glutamate, cysteine and glycine. Cysteine is the rate-limiting substrate for the synthesis within neurons. Most neuronal cysteine uptake is mediated by sodium-dependent excitatory amino acid transporter (EAAT) systems, known as excitatory amino acid carrier 1. Previous studies have demonstrated that EAAT is regulated by redox status, leading to impaired function by glutamate accumulation in the synaptic cleft during oxidative stress [31].

Oxidative stress can activate genes that encode the enzymes of antioxidant defence or transcription factors (nuclear factor κB, activator protein 1 and nuclear factor of activated T-cells) and many other structural proteins. The increase of Ca^2+^ in neurons can activate other enzymes, including protein kinase C (PKC), phosphatase, phospholipase, neuronal nitric oxide synthase and xanthine oxidase [26, 27].

The normalization of oxidative stress can represent a new experimental target in the treatment of disorders caused by excessive production of free radicals. Oxidative stress has been found in neurological disorders, including epilepsy, Parkinson’s disease, Down syndrome, Rett syndrome, autism and Alzheimer’s disease [32]. It has been demonstrated that neuronal damage due to oxidative stress and/or hyperadrenergic states can be prevented by treatment with free radical scavengers or specific compounds that act to prevent free radical production. It has been shown that neuroprotective therapy prevents neuronal damage in neurodegenerative diseases such as Parkinson’s disease and Alzheimer’s disease [33, 34]. Nutrient deficiencies are common in attention-deficit/hyperactivity disorder (ADHD). Supplementing the diet with minerals, vitamins, essential fatty acids omega-3 and omega-6, bioflavonoids and phosphatidylserine have been demonstrated to improve ADHD symptoms [35].

Currently, the pharmacological treatment used for FXS has limited effects on the symptoms observed in patients. Stimulants of the central nervous system, such as methylphenidate, are used to treat hyperactivity, and antipsychotic drugs, such as risperidone, are used to treat aggressive behaviour. Several drugs have been used to treat anxiety, such as alprazolam and lorazepam. Patients with epilepsy have been prescribed anticonvulsive drugs. In general, a drug or drug combinations are used to treat clinical symptoms, and there are no specific drugs that prevent the appearance of the disorders [36].

High-dose vitamin E supplementation may improve insulin action and decrease plasma fasting insulin and glucose levels by decreasing cellular oxidative stress, altering membrane properties and decreasing inflammatory activity [37]. Increased vitamin E intake may enhance the endogenous cellular antioxidant defence system and reduce levels of ROS that are produced by the mitochondria. Vitamin E can also act at the cellular level independently of its antioxidant activity and may potentially contribute to improved insulin action through the inhibition of PKC [38], the decrease of intracellular levels of diacylglycerol [39] and the activation of insulin substrate protein 1 [40].

Vitamin E has also been used in children. Most clinical data are available for α-tocopherol or tocopherol esters, such as α-tocopheryl acetate. The use of vitamin E to treat diseases such as abetalipoproteinaemia [41], cystic fibrosis [42–44], β-thalassaemia, sickle cell anaemia [45], inborn errors of metabolism [46], epidermolysis bullosa [47], glucose-6-phosphate dehydrogenase deficiency [48] and focal segmental glomerulosclerosis is well documented [49]. In many studies, the rationale for dosage has not been stated and dosing regimens have not been evaluated systematically. This is demonstrated by cystic fibrosis studies in children. Doses have differed among the studies: 5.5 to 47.4 IU/kg/day, 5 to 10 mg/kg/day and 50 to 100 IU/day [50, 51].

Vitamin C has also been used intensively in sick children; most available clinical data are for ascorbic acid or antioxidant combinations. The use of vitamin C is well documented in diseases such as aphthous stomatitis [52], infant burns [53], hyperlipidaemia and arteriosclerosis [54]. An oral dosage of 2,000 mg/m^2^/day of ascorbate may modulate the generation of ROS and augment neutrophil apoptosis, which could prevent neutrophil-mediated inflammation in children. A 12-month high-dose (30 mg/kg/day) trial of oral ascorbic acid was reported to be safe and well tolerated in children ages 2 to 16 years [55]. Vitamin C was also administered, as it enhances regeneration of oxidized vitamin E. Kinetic analysis and studies of vitamin E regeneration in a protein-denaturing system revealed that ascorbate regenerates vitamin E by a nonenzymatic mechanism, whereas glutathione regenerates vitamin E enzymatically. It has been suggested that significant interaction occurs between water- and lipid-soluble molecules at the membrane–cytosol interface and that vitamin C may function *in vivo* to repair membrane-bound oxidized vitamin E [56].

## Methods/Design

We designed a clinical trial to evaluate the effects of an antioxidant combination of ascorbic acid and α-tocopherol on the clinical condition of patients with FXS. The study includes patients from age 6 years up to age 18 with diagnosed FXS. This age limit was chosen because it is within this age range that a decline in hyperactivity and behavioural symptoms may occur. The minimum duration of treatment and follow-up for these patients is to be 6 months. The symptoms most easily measured are the presence and severity of behavioural abnormalities.

Here we present a new therapeutic approach to FXS that is based on the hypothesis that an increase in free radical production and a deficit in vitamins are involved in the pathology and that this often provokes severe comorbidity. Moreover, we take into account that current treatment protocols are frequently ineffective among young children and carry a risk for important potential side effects. Thus, we propose the following goals. (1) Our main goal is to test whether the combination of 10 mg/kg/day α-tocopherol and 10 mg/kg/day ascorbic acid reduces hyperactivity and behaviour abnormalities, improving cognition among patients between 6 and 18 years of age compared to placebo treatment. (2) Secondary goals are to assess the safety of the treatment, in terms of adverse events; to describe metabolic changes resulting from the treatment, as revealed by blood test results; and to measure the impact of this treatment on the quality of family and social life.

### Design

#### Type of clinical trial

This is a phase II, double-blind, randomized clinical study. It began in December 2011 and is currently in progress.

#### Recruitment of patients

The patients recruited will be those diagnosed with FXS according to molecular biology test who have currently presenting symptoms. Paediatric neurologists from the Andalusian region of Spain will be informed about the clinical trial so that patients can be referred to clinics where the study will be carried out. In order to maintain double-blind conditions, the doctors responsible for patient evaluation will be derived from the pharmacy department to be allocated to one of the two study groups according to a randomization program. Informed consent will be obtained from the patients’ parents or guardians (see Figure 1).

**Figure 1 Fig1:**
[figure not shown]
**Clinical trial flowchart.**

### Study subjects

Male patients ages 6 to 18 years with a diagnosis of FXS and clinical and behavioural symptoms of the disorder will be recruited.

### Selection criteria

#### Criteria for inclusion

Male patients ages 6 to 18 years: This is the age range during which the natural course of the condition is most exacerbated. Before the age of 6 years, hyperactivity may not yet have appeared. After age 18 years, behavioural symptoms tend to stabilize.Informed consent of the child’s parents or guardians and reasoned agreement with patients older than 12 years of age.Molecular diagnosis of FXS according to molecular biology criteria of having more than 200 CGG repeats and hypermethylation of the promoter region of the *FMR1* gene.Hyperactivity and behavioural symptoms of the disorder.

#### Criteria for exclusion

Severe neurological conditions not clinically controlled.Unrelated neurological disorders.Allergy to formula components (or excipient used).

#### Randomization criteria

Criteria set out above (age, diagnosis, consent).Current pharmacological treatment for behavioural symptoms.No contraindications due to the exclusion criteria.

Patients who fulfil these criteria will be included, randomly, in one of the two groups.

#### Randomization, blinding and assignment to treatment group

Randomization is centralized and performed immediately after the inclusion of an eligible patient. A software program will be used to ensure that allocation concealment is maintained within the pharmacy department at the Virgen de las Nieves Hospital (Granada). The randomization code will be kept concealed by the pharmacy department responsible for dispensing the corresponding medication. Randomization by blocks and stratification for confusion factors (age and concomitant medication) was performed to reduce bias (see Figure 2). Randomization to either the treatment group or the placebo group will be performed only when a patient with FXS is considered eligible to receive the medication included in this study and an informed consent form is signed by the caregiver.

**Figure 2 Fig2:**
[figure not shown]
**Randomization criteria for the trial.** Randomization by blocks and stratification for confusion factors (age and concomitant medication). T: Treated group, C: Control group.

#### Instrumentation

The clinical data and the results of the Wechsler Intelligence Scale for Children–Revised (WISC-R), the Conners Parent Rating Scale–Revised: Long Form (CPRS-R) [57], the Conners Teacher Rating Scale–Revised: Long Form (CTRS-R) and the Developmental Behaviour Checklist Short Form (DBC-P24) will be assessed at the baseline of the clinical condition (t0), at an intermediate time point after 12 weeks of treatment (t1) and at the end of the experimental period after 24 weeks of treatment (t2). The parents and/or guardians will be informed about the study details, and, upon receipt of their informed consent, the previously randomized medication will be provided. The medication is to be taken at the patient’s home, and a phone call follow-up is to be performed by the same neuropsychologist in charge of the evaluation at 30, 60, 120 and 150 days. Blood tests will be performed at the start (t0), intermediate time point (t1) and at the end of the experimental period (t2) for each of the 30 patients. The psychological impact of the treatment on the families concerned will be measured using the Spanish version of the Psychological General Well-Being Index–Revised (PGWBI-R).

#### Evaluations

The clinical diagnosis of FXS will be confirmed, and the Conners scale scores ascertained, so that the patient may be included in the study. Any subsequent decrease in the global score will be recorded (at t0, t1, t2). The DBC-P24, the WISC-R and metabolic changes in the blood test measurements will be recorded (at t0, t1, t2). The PGWBI-R score will be determined at t0, t1 and t2 of the study period.

#### Withdrawal of individual patients

Patients may withdraw from the study at any time for any reason and without any sanction for doing so. The researcher-collaborator, after consulting with the principal investigator and the study coordinator, may also interrupt the treatment program if the fact of continuing this treatment, in his/her opinion, is prejudicial to the patient’s welfare. If a patient withdraws or is withdrawn from the study, follow-up at day 90 should be continued whenever possible.

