#### Follow-up of patients who withdraw from the study

Any patients whose treatment is withdrawn will continue to be followed until the event in question is resolved or until, in the researcher’s opinion, important changes in the patient’s health state are unlikely to occur. The follow-up reports at 15, 30, 60 and 90 days will be completed for all patients who received medication (including placebo) during this study.

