#### Study periods

*Entry into the study (t0)*: The child’s parents and/or guardians agree to be included and sign the informed consent to enter into the clinical active phase of the study. The CPRS-R, CTRS-R, WSIC-R and DBC-P24 results will be assessed, taking into account that a score of at least 50 on the CPRS-R is a prerequisite for entry into the study. The baseline blood and urine analyses will be carried out for included patients. The PGWBI for the parents and guardians will be calculated.

*Intermediate period (12 weeks, t1)*: The CPRS-R, CTRS-R, WSIC-R and DBC-P24 scores will be calculated. The t1 blood and urine analyses will be carried out for included patients. The PGWBI scores for the parents and guardians will be calculated.

*End of study period (24 weeks, t2)*: The CPRS-R, CTRS-R, WSIC-R and also DBC-P24 are calculated. The T2 blood and urine analyses will be carried out for patients included in the study. The PGWBI for the parents/guardians will be calculated.

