#### General considerations

A descriptive statistical analysis will be performed using statistics of central trend and dispersion for the quantitative variables and frequency distributions for the categorical variables carried out separately for the experimental and control groups. The baseline variables will be compared using these techniques. A flow diagram will be drawn to show the sequence from the initially eligible population to those excluded from the study (refusals, dropouts, lost to follow-up and so forth) in accordance with the criteria in the CONSORT guidelines.

A comparison will be made of between-group differences in the initial and final measurements for the diverse elements of the CPRS-R, CTRS-R and DBC-P24 using unpaired nonparametric tests. For the final within-group comparison, paired nonparametric tests will be used for nonparametric repeated measures with adjustments for baseline imbalances and scores. The same analysis will be performed for the index of psychological well-being to measure the repercussions of the treatment on family life.

The principal outcome variable (POV) will be taken as the change in global score on the Conners scales, adjusted for the baseline values. A simple linear regression model will be constructed for this POV, and the level of significance will be set at *P* < 0.05. Subsequently, a multiple linear regression model will be created, including the variable ‘Experimental/Control Group’ and adjusting for any baseline variables that may be unbalanced. Statistical adjustment will be performed by means of a multivariate model including the variable group (experimental and control) and concomitant treatment (yes or no). The safety of the treatment will be described in terms of the percentage of adverse effects.

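### The follow-up named for patients who stop runs to day 90, fits no other schedule in the protocol, and requests no 24-week Conners score

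*Protocol article*

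**What the plan says.** Two adjacent sections of the protocol article deal with patients who stop.

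- Withdrawal of individual patients covers both patients who leave of their own accord and those whose treatment the researcher interrupts. It then gives one rule for all of them: "If a patient withdraws or is withdrawn from the study, follow-up at day 90 should be continued whenever possible".
- The section after it, headed Follow-up of patients who withdraw from the study, says that patients taken off treatment "will continue to be followed until the event in question is resolved", or until the researcher expects no further important change in health. It continues: "The follow-up reports at 15, 30, 60 and 90 days will be completed for all patients who received medication (including placebo) during this study".

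Other sections set different times.

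- Instrumentation: "a phone call follow-up is to be performed by the same neuropsychologist in charge of the evaluation at 30, 60, 120 and 150 days".
- Instrumentation, Evaluations and Study periods place the Conners parent and teacher scales at t0, 12 weeks (t1) and 24 weeks (t2).
- The opening of Methods/Design sets at least 6 months of treatment and follow-up.

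On analysis, General considerations states: "A comparison will be made of between-group differences in the initial and final measurements for the diverse elements of the CPRS-R, CTRS-R and DBC-P24". It defines the principal outcome separately, as baseline-adjusted change in the global Conners score, without naming a week.

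**The concern.** The trial runs for 24 weeks, but the only follow-up days named for someone who stops end at day 90. The single open-ended element is tied to an adverse event and carries no efficacy scale. A site that follows these two sections literally has no instruction to obtain a t2 Conners score once treatment has stopped.

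Patients who stop because of side effects or lack of benefit are unlikely to resemble those who continue. If their final scores are missing, the comparison at 24 weeks can lose part of the protection that randomisation gives. A later analysis plan can choose a model for missing data, but it cannot recover scores that were never collected. The place to settle this is therefore the protocol. With 15 patients per arm, each lost patient carries weight.

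**Working it through.** **1. The schedules side by side.** In days, t1 = 12 × 7 = 84 and t2 = 24 × 7 = 168.

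| Section | Contact | Days |
|---|---|---|
| Instrumentation; Study periods | Conners scales | 0, 84, 168 |
| Instrumentation | Phone calls | 30, 60, 120, 150 |
| Follow-up of patients who withdraw | Reports, all who received medication | 15, 30, 60, 90 |
| Withdrawal of individual patients | Follow-up after withdrawal | 90 |

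The report schedule shares only days 30 and 60 with the calls, and no day with the Conners assessments. It is written for everyone who received medication, so the mismatch also affects patients who stay in the trial.

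**2. Does the unstated time origin resolve it?**

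- Counted from entry, day 90 falls 90 − 84 = 6 days after t1 and 168 − 90 = 78 days before t2, at 90/168 = 54% of the period.
- Counted from withdrawal on day w, follow-up reaches t2 if w + 90 ≥ 168, that is, if w ≥ 78. Patients who stop earlier fall short. Those who stop later are followed long enough, but still without a stated Conners assessment.

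Neither reading supplies a request for the t2 score.

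**3. What the dropout allowance covers.** The section on statistical power and sample size takes 13 per group and 10% dropout. 13/(1 − 0.10) = 14.4, rounded up to 15 per group, or 30 in total. The plan's inflation step is reproduced. The base of 13 cannot be, because no effect size or SD is given. Expected loss is 0.10 × 30 = 3 patients. Losing 2 in each arm still leaves 13 per arm, so the allowance covers precision at the planned loss. It has no bearing on whether those lost differ from those who remain.

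**4. Illustration of possible bias (assumed inputs).** If k of 15 patients in one arm have no t2 score, and would on average have scored δ SD worse than the rest of their arm, the mean of the remaining patients differs from the full-arm mean by (k/15) × δ.

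| k lost of 15 | δ = 0.5 SD | δ = 1 SD |
|---|---|---|
| 1 | 0.03 | 0.07 |
| 2 | 0.07 | 0.13 |
| 3 | 0.10 | 0.20 |

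The bottom row puts the whole planned loss into one arm. With losses in both arms, the treatment difference moves by the difference between the two arms' shifts, which may partly cancel.

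For scale only: 13 per group at two-sided 0.05 and power 0.8 corresponds, by the normal approximation, to a standardised difference of (1.96 + 0.84) × √(2/13) = 1.10. The range above is then 0.033/1.10 = 3% to 0.20/1.10 = 18% of that. The 1.10 is back-solved and is not stated in the protocol.

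**The case against.** The strongest reply is that the two withdrawal sections are safety follow-up: they speak of welfare, event resolution and health state. Nothing there says that contact ends at day 90 or that the Conners scales are dropped. Day 90 can be read as a minimum, the event follow-up has no end date, the opening of Methods/Design sets 6 months, and the Conners schedule exempts nobody. This stands in part. A reader might infer that the protocol forbids or ends outcome collection at day 90, and the text does not go that far. What remains is that the named days conflict with every other schedule and that no sentence tells a site to obtain t2 after treatment stops.

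A reader might also infer a completers' analysis in which a patient who leaves after week 12 contributes nothing. The documents do not establish this. The sentence on initial and final measurements concerns between-group comparisons of the scales' various elements. The principal outcome has its own sentence with no week named, repeated measures are mentioned for the within-group comparison, and the analysis population may be fixed in a plan that is not shown. Restricting reports to patients who received medication is ordinary for safety and does not define the efficacy population.

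Nor can the bias be expressed as a firm share of the treatment effect. The Discussion cites standardised effects of 0.30 and 3.94 for another compound. A 0.13 SD shift is 44% of one and 3% of the other, and neither is this trial's target. The loss of precision in going from 15 to 13 per arm is already planned for.

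Finally, families who withdraw consent cannot be followed, so the remedy reaches only those who stop treatment and stay in contact. That limits the gain but does not remove it.

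**Conclusion.** The point holds as a conflict in a stated rule, not merely as a missing detail. The post-withdrawal schedule fits neither the calls nor the assessments, has no time origin, merges two different events, and leaves the t2 Conners score unrequested after treatment stops. Followed literally, it can produce selectively missing 24-week outcomes.

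Taking 24 weeks as the time of the final outcome is itself a reading: it rests on t2 being the end of the study and on the comparison of initial with final measurements. The amount of bias is unknown. The range of 0.03 to 0.20 SD in one arm's mean depends wholly on the assumed 1 to 3 leavers of 15 and the assumed deficit of 0.5 to 1 SD. This is a phase II pilot and about three patients are expected to leave. The matter should be corrected because it is cheap to prevent and cannot be repaired afterwards, not because a large distortion has been shown.

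**What to change.** - Reconcile the two withdrawal sections with the opening of Methods/Design, Instrumentation and Study periods, and state the day from which each follow-up time is counted. Which safety contacts are needed is for the investigators to decide.
- Separate stopping trial treatment from withdrawing consent to follow-up.
- State that the CPRS-R and CTRS-R are collected at the scheduled t1 and t2 dates for every randomised patient whose family still consents, whether or not treatment continues, and that these patients are analysed in their allocated group.

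The choice of longitudinal model can be left to the analysis plan.

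The cost is a short amendment and a few extra questionnaires for about three patients. The teacher scale also needs the school's continued cooperation. The sample size of 30 does not change.
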